## Abstract

*Background*: Promotion of a healthy lifestyle is considered a good strategy for dealing with chronic diseases. Mobile-based lifestyle interventions have shown beneficial effects in the control and treatment of chronic diseases such as diabetes, obesity and metabolic syndrome. Current clinical trials for mobile-based lifestyle intervention were mainly conducted among non-elderly populations, thus well-designed trials performed among the elderly who are more susceptible to chronic diseases are needed. The study aims to assess the effect of the mobile-based lifestyle intervention on the improvement of body weight, glucose and lipid metabolism among overweight and obese elderly adults in China. *Materials and Methods*: Participants aged 60–80 years who are overweight or obese will be randomly assigned to receive mobile-based nutrition and exercise intervention, mobile-based exercise intervention and no intervention for 3 months. Before the intervention, participants will receive the training of the mobile application and sports bracelet. The primary outcome will be the between-group (three groups) difference in body mass index at the end of intervention. The secondary outcomes will include body composition, parameters of glucose and lipid metabolism, blood pressure, dietary data and physical activity data. All these outcomes will be assessed at baseline, day 45 and day 90. *Ethics and dissemination*: The trial has been approved by the Ethics Committee of Peking University Health Science Center (IRB00001052-18039).

## 1. Introduction

Overweight and obesity have increased globally and substantially in recent years [1]. In China, the prevalence of overweight and obesity increased from 37.4% and 8.6% to 41.2% and 12.9%, respectively, which has become a major public health problem [2]. These conditions are proved to be associated with chronic diseases such as hypertension, diabetes, non-alcoholic fatty liver disease, coronary artery disease and dyslipidemia and cause a reduction of life expectancy [3]. 

Aging is also a risk factor for many chronic diseases, due to the decline of physiological functions in the elderly. Chronic diseases have become a great health threat to elderly residents in China. The prevalence rates of hypertension, diabetes and hypercholesterolemia in China were 58.3%, 19.4% and 10.5%, respectively, among people older than 60 years old, which were higher than that of people less than 60 [4]. According to the data from the National Bureau of Statistics, the number of Chinese people aged 65 or over in 2019 was 176 million, which represents 12.6% of the whole population of China. With the increasing aging population, the healthy and economic burden created by chronic diseases can be expected to become more and more serious. 

These chronic diseases which are major causes of morbidity and mortality have been considered to be closely related to changes in dietary and lifestyle [5]. As a result, the promotion of a healthy lifestyle has been seen as a key strategy of reducing such chronic diseases [3]. A lot of studies have demonstrated that lifestyle intervention has a beneficial effect on reducing the diabetes incidence among impaired glucose tolerance patients [6] and improvement of obesity [7], hypercholesterolemia [8], hypertension [9], non-alcoholic fatty liver disease [10] and metabolic syndrome [11]. However, in the traditional types of lifestyle intervention programs, patients usually need to communicate with a clinician or qualified nutritionist in community health centers or physician’s offices, thus the traditional lifestyle intervention through in-person education programs is resource intensive [12]. In addition, the effect of traditional lifestyle intervention decreases or even disappears after several years [13], which may be because it is hard to change people’s lifestyle [6]. 

Advances in mobile technology make it possible to supply health management support to patients which is both convenient and cost-effective [12]. Mobile applications (apps) for health management have been shown to play a positive role in improving several chronic diseases and may bring enormous social and economic benefits. Kumar et al. found that mobile-based lifestyle intervention could decrease the hemoglobin A1c level of Type 2 diabetes patients significantly [14]. An American study conducted among patients with obesity, hypertension, diabetes and hyperlipidemia showed that mobile-based interventions produced larger weight loss compared with the control group during the whole 12-month follow-up [15]. Another study demonstrated that overweight and obesity Korean patients, after following a mobile-based lifestyle intervention, had a clinically significant weight loss and maintained this effect during the 52-week follow-up and also showed significant improvement in metabolic syndrome parameters such as fasting glucose levels and blood lipids [16]. 

The overweight and obese elderly populations with two risk factors, aging and high-BMI, are more susceptible to chronic diseases. However, most clinical trials for mobile-based lifestyle intervention were conducted among non-elderly populations [14,15,16,17]. Considering the data on the effect of mobile-based lifestyle intervention on the control of chronic diseases among the elderly population was very limited, well-designed randomized controlled trials (RCTs) performed in the elderly are needed. 

The purposes of this study are, first, to assess the effect of the mobile-based lifestyle intervention on the improvement of body weight, glucose and lipid metabolism among overweight and obese elderly adults in China. In addition, to explore whether the mobile-based lifestyle intervention may have an effect on blood pressure, body composition, C-reactive protein, liver enzymes, uric acid and the factors associated with blood glucose or lipid including copeptin, irisin and adiponectin. Third, to compare differences between males and females. Finally, to provide suggestions for the intelligent health management among the elderly in China.

## 2. Materials and Methods

### 2.1. Sample Selected

The recruitment of the study subjects will take place in communities through advertisements in five cities (Jinan, Taiyuan, Nanchang, Hefei, and Guangzhou) in China. After recruitment, basic information such as social demographics, disease history, drug use and family history will be collected.

Subjects eligible for this trial must meet the following inclusion criteria: (1) age between 60–80 years old; (2) body mass index (BMI) ≥ 24; (3) living or working in Jinan, Taiyuan, Hefei, Nanchang and Guangzhou and (4) ability to use smart phones. The exclusion criteria will include: (1) participation in any activities related to weight management; (2) diagnosed with psychiatric disorder such as cognitive dysfunction, schizophrenia or depression; (3) with pacemakers or other medical electronic devices; (4) with walking disability; (5) history of surgical treatment of obesity; (6) excessive drinking and (7) unwillingness to change their habits. 

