### 2.4. Intervention

Volunteers allocated to Group A and B will have access to a health management app. The app has functions of recording and monitoring the participants’ diet and exercise daily. The interventions include mobile-based nutrition interventions and exercise interventions. 

The nutrition interventions require the subjects be provided with 20 g of the professional meal replacement powders (Huaruizhongjian Biotechnological Co., Ltd., Shandong, China), 200 mL milk and 5 mL flaxseed oil for their breakfast and dietary guidance based on Mediterranean diet for their lunch and supper. The meal replacement powders include 10 g of meal replacement powders rich in minerals (4.50 g protein, 0.09 g fat, 1.26 g carbohydrate and 3.00 g dietary fiber with 125 kJ in total energy) and 10 g of meal replacement powders rich in vitamins (4.65 g protein, 0.11 g fat, 1.05 g carbohydrate and 3.18 g dietary fiber with 126 kJ in total energy). The dietary guidance will be through individual sessions with nutritionists using mobiles, including healthy food choices and portion sizes, 3 to 5 times per week depending on the participants’ compliance. The diets will be tracked and recorded through uploading the food logs and pictures of their three meals per day using the health management app under the supervision of the investigators in the background. 

The exercise interventions require the subjects be provided with exercise guidance and complete around 20 min of aerobic exercise, 20 min of resistance exercise and at least 6000 steps every day. The exercise guidance will be through individual sessions with exercise instructors, including exercise choices, duration and intensity, 3 to 5 times per week depending on the participants’ compliance. If the participants feel a little tired after the exercise and comfortable for the next day, the exercise intensity will be the best. The everyday steps of the subjects will be tracked and recorded through the sports bracelet and the aerobic exercise and resistance exercise logs and pictures will be uploaded using the mobile app, which will be supervised by the investigators in the background. 

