### 2.6. Procedures

A summary of this trial is presented in Table 1. The study will consist of three stages:

Stage 1: from enrollment to the start of the intervention. At enrollment, eligible participants will sign informed contents and their basic information will be collected. Then they will be randomly divided into three groups (Group A, B and C). Participants in Group A and B will be taught how to use the app and sports bracelet by the researchers and required to record their diets and physical activities using the app and bracelet following their usual way of life for one week.

Stage 2: from the start of intervention (day 0) to day 44. On the morning of day 0, participants will be asked to arrive at the lab at 7:00 a.m. Measurements including anthropometry, body composition, blood pressure, fasting blood samples, dietary and physical activity data will be obtained based on standard procedures. Then, participants in Group A will receive mobile-based nutrition and exercise intervention. Participants in Group B will receive mobile-based exercise intervention. Participants in Group C will receive no interventions.

Stage 3: from day 45 to day 90. On the morning of day 45, measurements including anthropometry, body composition, blood pressure, fasting blood samples, dietary and physical activity data will be performed as day 0. Then, Group A and B will continue to receive their respective intervention and Group C will receive no intervention as before. On the morning of day 90, anthropometry, body composition, blood pressure, dietary and physical activity data will be measured and fasting blood samples will be collected for the third time. 

**Table 1 ijerph-18-04854-t001:** Summary of the trial.

Time Point	At Enrollment	After Allocation		
		Start (Day 0)	Day 45	Day 90
Enrolment				
Eligibility screen	√			
Informed consent	√			
Collection of basic information	√			
Randomization	√			
App and sports bracelet training	√			
Interventions (day 0-day 90)		√	√	√
Follow-up (day 0-day 90)		√	√	√
Assessments				
Anthropometry	√	√	√	√
Body composition (Inbody measurement)		√	√	√
Blood lipids		√	√	√
Fasting and postprandial blood sugar		√	√	√
Hemoglobin A1C		√	√	√
Blood CRP and insulin		√	√	√
Blood ALT and AST		√	√	√
Blood uric acid		√	√	√
Blood copeptin		√	√	√
Blood irisin		√	√	√
Blood adiponectin		√	√	√
Blood pressure		√	√	√
Dietary data		√	√	√
Physical activity data		√	√	√

CRP: C-reactive protein; ALT: alanine aminotransferase; AST: aspartic transaminase.

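### The printed exclusion list does not settle fitness for the required exercise (Groups A and B) or tolerance of the study foods (Group A), so unsuitability can surface after randomisation and differ by arm

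*Protocol article*

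**What the plan says.** **Eligibility (protocol article, 2.1).** Seven numbered exclusions are printed. The first two concern taking part in other weight-control efforts and having a psychiatric diagnosis. The next three are "3) with pacemakers or other medical electronic devices; (4) with walking disability; (5) history of surgical treatment of obesity". The last two concern heavy alcohol use and reluctance to alter one's way of life.

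The same section states that "basic information such as social demographics, disease history, drug use and family history will be collected".

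**Intervention (2.4).** Groups A and B must "complete around 20 min of aerobic exercise, 20 min of resistance exercise and at least 6000 steps every day". Group A also receives 20 g of meal replacement powder with "200 mL milk and 5 mL flaxseed oil for their breakfast". Group C receives neither the exercise nor the foods.

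**Order of events (2.6 and Table 1).** Consent, the eligibility screen, collection of basic information and randomisation all take place at enrolment. The intervention starts a week later, on day 0.

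**After randomisation.** Section 2.5 has participants who do not meet the study's requirements leave the trial. The quality-control text in section 4 adds that the data of a participant who fails the requirements are eliminated and the reason recorded.

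**The concern.** The eligibility list and the intervention were not written to fit each other. A person who can walk unaided and has no implanted device may still be unable to take daily aerobic and resistance training. A person may also be unable to take milk, the powder or the oil. Neither is excluded by the printed list, so either may be randomised.

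Two things are at stake. One is safety: an older participant may be set a regimen for which no printed rule has checked suitability. The other is comparability. The exercise can be failed only in A or B, and the foods only in A. If failing a requirement leads to discontinuation and loss of data, removal after randomisation depends on the assigned arm. That weakens the comparability of the three groups that section 4 counts as a strength of the design.

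**Working it through.** **1. Exclusions set against requirements.**

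| Requirement | Arms | Printed exclusion that bears on it |
|---|---|---|
| Daily aerobic and resistance exercise, step target | A, B | Electronic devices; walking disability (partial cover) |
| Powder, milk, flaxseed oil at breakfast | A only | None |
| Routine lifestyle | C | Not needed |

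The other items (weight-management activity, psychiatric disorder, obesity surgery, excessive drinking, unwillingness to change habits) do not address either requirement. Unwillingness is not inability.

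**2. What is known before randomisation.** Disease history and drug use are taken at enrolment, ahead of allocation. No printed criterion uses them to judge suitability for the exercise or the foods. The information needed for a check is therefore largely at hand, but no rule acts on it.

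**3. What happens to someone found unsuitable later.** By 2.5 the person discontinues, and by section 4 the data are eliminated, if not meeting the requirements is read to include not following the regimen. The article does not define the term. On that reading the same person would be removed from A or B for the exercise, or from A for the foods, but not from C on either ground.

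**4. The plan's own sample size (2.8).** Inputs: mean BMI changes −2.8, −2.5 and −0.9 kg/m², SD 1.4, two-sided 0.05, power 0.90. One-way ANOVA power from the noncentral F distribution is 0.873 at n = 12 and 0.901 at n = 13 per group, so the stated 13 is reproduced. Then 13 + 26 = 39, 39 × 5 = 195 (stated as about 200), and 200 / (1 − 0.20) = 250. The dropout allowance is 250 − 200 = 50 per group. These figures are not in dispute.

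**5. Possible shift in the contrasts (illustration only).** The documents give no share of unsuitable participants. Let q be the fraction of an intervention group removed and d the difference in mean BMI change between those removed and those kept. The mean of those kept then differs from the mean of all randomised by q × d. With C complete, A–C or B–C shifts by the same amount.

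| q (assumed) | Removed, of 250 | d = 0.5 | d = 1.0 |
|---|---|---|---|
| 2% | 5 | 0.01 | 0.02 |
| 5% | 12.5 | 0.025 | 0.05 |
| 10% | 25 | 0.05 | 0.10 |
| 20% | 50 | 0.10 | 0.20 |

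Shifts are in kg/m². The largest, 0.20, is one fifth of the 1 kg/m² that 2.8 calls clinically meaningful. The A–B contrast is relatively more exposed: its planned difference is only −2.5 − (−2.8) = 0.3 kg/m², and food-related removal falls on A alone. At q = 5% and d = 0.5 the shift is 0.025 / 0.3, about 8% of that difference. At q = 10% and d = 1.0 it is 0.10 / 0.3, about 33%.

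**The case against.** **This is a condensed article.** The verb introducing the exclusions can be read as non-exhaustive, and the full protocol approved by the ethics committee is not shown. It may hold a longer list. This stands as a limit, but it does not dispose of the point. The article prints a numbered list, a required daily regimen, a visit order and a data-elimination rule, and these stated rules do not fit together. If a fuller list exists, the printed one should be reconciled with it.

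**The exercise is individualised.** Instructors guide choice, duration and intensity 3 to 5 times a week, intensity is judged by how the participant feels, and anyone may withdraw on request. This softens the exposure. It acts only after allocation, however, and does nothing about the foods.

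**Stronger readings the documents do not support.**
- A reader might infer that blood pressure and glucose are measured too late, because Table 1 first lists them on day 0, after allocation. No eligibility criterion uses either value. Section 2.6 also puts the day-0 measurements ("Measurements including anthropometry, body composition, blood pressure, fasting blood samples, dietary and physical activity data will be obtained based on standard procedures") before the intervention begins. They are baseline outcome measurements, not a misplaced screen, and an earlier reading with no rule attached would change nothing.
- A reader might apply the over-60 figures in the Introduction ("prevalence rates of hypertension, diabetes and hypercholesterolemia in China were 58.3%, 19.4% and 10.5") to the 500 people in A and B: 500 × 0.583 ≈ 292 with hypertension and 500 × 0.194 = 97 with diabetes. These count people the trial means to enrol. Most would not be unsuitable, and the figures do not estimate harm.
- A reader might conclude that unsuitable people will in fact be exposed or lost, or that the food issue touches both intervention groups. The text shows only that exposure or loss can happen, and the foods go to Group A alone.

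**Conclusion.** The point holds as a mismatch between stated rules. Beyond electronic devices and walking disability, the printed exclusions do not settle whether a candidate can take the exercise required in A and B, and they say nothing on tolerance of Group A's foods. Combined with discontinuation and data elimination, this permits avoidable exposure and removal that depends on arm.

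The likely bias in A–C and B–C is small, 0.01 to 0.20 kg/m² under the assumed ranges. It arises only if the elimination rule is applied to people who cannot follow the regimen. A–B could be affected more in relative terms, again only under assumption. Participant safety and the comparability of the randomised groups, rather than power, make the change worth making.

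**What to change.** Reconcile sections 2.1, 2.4, 2.5, 2.6 with Table 1, and 4:

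1. State in 2.1 that suitability for the exercise and for the study foods is settled before randomisation, in the same way for every candidate whichever arm follows, using the history already collected at enrolment. The sponsor's clinicians set the clinical content; none is proposed here.
2. Show this check in Table 1 as part of the existing eligibility screen, ahead of randomisation.
3. Define in 2.5 and section 4 what failing the requirements means. Separate stopping the intervention, a clinical decision, from keeping the data, so that participants found unsuitable after randomisation are not removed from the data by arm.
4. If the full protocol already contains such a check, align the published list with it.

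The cost is a protocol amendment and two questions at a visit that already takes place. The downside is a slightly narrower study population.

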### 2.2. Study Design

This study is designed as a prospective, open-labeled, randomized, controlled and multi-center trial. Eligible subjects will be randomly assigned to three groups: the mobile-based nutrition and exercise intervention group (Group A), mobile-based exercise intervention group (Group B) and no intervention group (Group C). This study will assess parameters of glucose and lipid metabolism for three times. In addition, weight, height, waist circumference, hip circumference, blood pressure, C-reactive protein, liver enzymes, uric acid, copeptin, irisin, adiponectin, dietary data and physical activity data will also be evaluated at the same time. The study design is shown in Figure 1.

### 2.3. Randomization and Blinding

All participants will be assigned to three groups according to a random number table with a 1:1:1 allocation ratio. The assignment will be enclosed in sealed, opaque, numbered envelopes by an investigator not involved in subject assessment and recruitment. Because of the nature of the intervention, it is not possible to blind participants and study investigators to the group allocation. To minimize bias, at every visit, outcome assessors will be blinded to group allocation and objective clinical measures will be measured. Investigators who analyses the data will also be blinded to the data collection and data entry, as each subject will be identified by a random number.

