### 2.8. Sample Size Calculation

The sample size was calculated for a one-way analysis of variance (ANOVA) comparing the mean change in between-group (three groups) BMI from preintervention to postintervention. According to related researches, the clinically meaningful difference in change in BMI was set to 1 kg/m^2^ and the mean change in BMI of the 12-week diet and exercise group, the 12-week exercise group and the control group was −2.8, −2.5 and −0.9 kg/m^2^, respectively. The standard deviation (SD) was assumed to be equal for all three groups and was set to SD = 1.4 Kg/m^2^ [29,30]. To obtain a power of 0.90 for the overall test of differences in means, using a significance level of 0.05, 13 individuals are required in each group. To account for the three stratification groups (age: 60~66, 67~73 and 74~80), a further 26 individuals are required. Considering the study will be conducted in 5 centers, approximately 200 individuals are required for each group. To account for 20% dropout, approximately a total of 250 individuals are required for each group. Calculations were performed using PASS statistical software Version 15.0.2 (NCSS, Kaysville, UT, USA).

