### 2.9. Statistical Analysis

Continuous data will be first tested for normal distribution using the Kolmogorov-Smirnov test and presented as mean ± standard deviation (SD) if normally distributed, or median [interquartile range (IQR)] if not. Categorical data will be presented as percentages.

The effect of mobile-based lifestyle intervention on BMI, parameters of glucose and lipid metabolism, body composition, C-reactive protein, liver enzymes, uric acid, copeptin, irisin, adiponectin and blood pressure among the three groups will be investigated by One-way ANOVA or Kruskal-Wallis H test. 

*p* values will be two-tailed and differences will be considered significant at *p* < 0.05. All analyses will be performed using SPSS software Version 23.0 (SPSS Inc., Chicago, IL, USA).

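### The sample size is built on 15 age-by-centre cells, but Section 2.3 names no stratification, the tests in Section 2.9 can hold neither factor, and the Discussion adds age but not centre

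*Protocol article*

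**What the plan says.** Four places in the protocol article bear on the role of age band and centre.

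- **Section 2.8 (sample size).** After a base figure of 13 per group: "To account for the three stratification groups (age: 60~66, 67~73 and 74~80), a further 26 individuals are required". Then: "Considering the study will be conducted in 5 centers, approximately 200 individuals are required for each group". A 20% dropout allowance takes this to about 250 per group.
- **Section 2.3 (randomisation).** Participants are assigned "according to a random number table with a 1:1:1 allocation ratio", with the assignments held in sealed, opaque, numbered envelopes. No stratification factor is named.
- **Section 2.9 (analysis).** The effect on BMI and the other listed outcomes across the three groups "will be investigated by One-way ANOVA or Kruskal-Wallis H test". No stratum, centre or covariate is mentioned.
- **Section 4 (Discussion, paragraph on strengths and limitations).** Age appears in a list of potential confounders that are to enter the analyses as covariates. Centre or city is not in that list.

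**The concern.** Age band and centre are the whole reason that the sample size rises from 13 to about 200 per group. Factors that matter that much to the size of a trial would be expected in its allocation, its analysis, or both. Here the allocation section names neither, the analysis section fixes tests that can take neither, and the Discussion brings in one of the two in a way that those tests cannot carry out.

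Two things are at stake. First, a reader cannot tell what the primary BMI analysis is: an unadjusted comparison of three groups (Section 2.9) or a covariate-adjusted one (Section 4). Second, if centre or age is related to BMI change, a model without them leaves that variation in the error term. If allocation is also not stratified, the arms may be uneven within the cells for which the trial was sized.

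**Working it through.** **1. Reproduce the plan's figure.** Inputs, all from Section 2.8:

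- Test: "The sample size was calculated for a one-way analysis of variance (ANOVA) comparing the mean change in between-group (three groups) BMI".
- Mean changes, in the order diet and exercise, exercise, control: "the control group was −2.8, −2.5 and −0.9 kg/m^2^, respectively".
- Spread: "The standard deviation (SD) was assumed to be equal for all three groups and was set to SD = 1.4 Kg/m^2".
- Target, stated per group: "To obtain a power of 0.90 for the overall test of differences in means, using a significance level of 0.05, 13 individuals are required in".

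The noncentrality is λ = n·Σ(μᵢ − μ̄)²/SD², with 2 and 3(n − 1) degrees of freedom.

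- μ̄ = (−2.8 − 2.5 − 0.9)/3 = −2.067
- Σ(μᵢ − μ̄)² = 0.538 + 0.188 + 1.361 = 2.087
- λ = n × 2.087/1.96 = 1.065n

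Power is 0.873 at n = 12 and 0.901 at n = 13, so 13 per group reproduces.

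**2. Reproduce the inflation.**

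- 13 + 26 = 39 = 13 × 3 age bands
- 39 × 5 centres = 195, stated as about 200
- 200/(1 − 0.20) = 250

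The sample size is therefore 13 per arm in each of 3 × 5 = 15 age-by-centre cells. The two factors account for a 15-fold increase (195/13).

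**3. Set the sections side by side.**

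| Factor | Sizing (2.8) | Allocation (2.3) | Analysis (2.9) | Discussion (4) |
|---|---|---|---|---|
| Age | 3 bands, called strata | not named | not in the test | covariate |
| Centre | 5 centres | not named | not in the test | not named |

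A one-way ANOVA has a single factor, and a Kruskal-Wallis test compares groups only. Neither can include age as a covariate, so Sections 2.9 and 4 cannot both hold as written. For centre there is no conflict, only absence: it drives the size and is used nowhere in the analysis.

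**4. Imbalance if allocation were unrestricted.** This is conditional on two assumptions that the article does not settle: no stratification or blocking, and equal centres and age bands. The count per arm among N is then Binomial(N, 1/3), with SD = √(N × 1/3 × 2/3).

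| Unit | N | Expected per arm | SD | 95% range |
|---|---|---|---|---|
| Whole trial | 750 | 250 | 12.9 | 225–275 |
| Centre | 150 | 50 | 5.8 | 39–61 |
| Age-by-centre cell | 50 | 16.7 | 3.3 | 10–23 |

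With 600 completers there are 40 per cell and 13.3 per arm. By simulation, a given arm then falls below 13 in about 40% of cells, and at least one arm does in about 94%. With all 750 counted, the figures are about 10% and 31%. The completer figures are high partly because 13 lies just under the expected 13.3.

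**5. Precision and power.** If centre and age explain a share R² of outcome variance, the standard error is multiplied by √(1 − R²). With R² assumed at 5–10%:

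- √0.95 = 0.975, a reduction of 2.5%
- √0.90 = 0.949, a reduction of 5.1%

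At 200 per arm and SD 1.4, the 95% half-width of a pairwise difference is 1.96 × 1.4 × √(2/200) = 0.274 kg/m². With adjustment it is 0.260–0.267 kg/m².

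Overall F-test power at 200 per group, on the plan's inputs, is above 0.999. It stays there after 6 degrees of freedom are spent on age band (2) and centre (4).

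**The case against.** The strongest reply has three parts.

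**Silence is not a statement.** A reader might infer from Section 2.3 that one simple, unstratified list serves the whole trial. The section does not say so. It is silent on strata, on blocks and on whether each centre has its own list, and a journal article commonly leaves such detail to the full protocol. The wording in Section 2.8 even fits a stratified allocation that was condensed out of Section 2.3, or planned analyses within age bands that have nothing to do with allocation. This stands. The imbalance figures are therefore conditional, and the request is to state the method.

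**Age is not ignored.** A reader of Section 2.9 alone might conclude that the analysis uses neither factor. Section 4 commits to age as a covariate, so that conclusion is wrong for age. What remains is a contradiction between the two sections about age, and the absence of centre from both. The list in Section 4 is introduced as examples, so centre is not excluded, but nothing in the article names it.

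**The harm is small.** Random allocation without strata does not bias the comparison, overall power is ample, and an assumed 5–10% variance share moves the pairwise half-width by about 0.01 kg/m² against a stated meaningful difference of 1 kg/m². The article also gives no figure for how much centres differ. This stands too, and it limits the weight of the point. It does not reconcile the sections.

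**Conclusion.** The point holds as a mismatch between sizing, allocation and analysis. The trial is sized for 15 age-by-centre cells, the randomisation section names neither factor, and the named tests can accommodate neither. The Discussion contradicts those tests on age and omits centre. This follows from the text and from arithmetic that reproduces exactly.

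Its size is modest: about 2.5–5% in standard error under the assumed 5–10% variance share. Any imbalance within centres or cells depends on unrestricted allocation and equal cells, neither of which the article establishes. The documents do not support the stronger reading that the trial is underpowered or its comparison biased. The change is worth making because it costs almost nothing, settles which BMI analysis is intended, and makes the analysis reflect the factors on which the sample size rests.

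**What to change.** 1. **Section 2.9.** Replace the one-way ANOVA for BMI with a linear model (ANCOVA) of group, with centre and age band (60–66, 67–73, 74–80) as fixed factors. The Kruskal-Wallis test cannot carry these factors, so it should not stand in for this model.
2. **Section 4.** Align the covariate statement with that model, so that age has the same role in both places and centre is named.
3. **Section 2.3.** State whether allocation is stratified by centre and age band. If it is not, and allocation has not begun, use permuted blocks within centre (and age band). Block sizes should vary and be concealed, because fixed small blocks in an open-label trial make upcoming assignments predictable.
4. **Section 2.8.** If allocation is complete and was not stratified, keep steps 1 and 2, and describe the age bands and centres as analysis or subgroup cells rather than as strata. The steps from 13 to 39 to about 200 then still have a stated reason.

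The cost is two extra factors in one model (6 degrees of freedom) and some rewording. If stratified allocation is adopted, it also needs five envelope series (by centre) or fifteen (by centre and age band). Stratification evens out the arms within a cell but does not fix how many people are recruited into it. The planned sample size does not change.
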